| Medical Record Review                  |                     | 
participants will be coded as having attempted suicide during the timeframe assessed. For suicide attempts, the SASII will assess the method used, intent to die, highest level of medical treatment received, and greatest potential lethality of all self-directed violence in a specified time period (Linehan et al., 2006). A lifetime version will be administered at baseline. A recent version assessing only the time since the last assessment will be administered at future assessments.
 
Clinical interviews will be supplemented by a medical record review to identify medically documented SAs during follow up that may have been missed in our interviews because they were not reported by participants or were unknown due to participant nonresponse or unavailability.
                                                                                                                                                                                                                                                                                                                                                                                                                                                                                                                                                                                                                                                                      |                                             |

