#### **11.1.3 Justification of sample size-suicide attempts**

Power and sample size calculations were made in nQuery, Version 8.7.2. Initial sample size calculations for suicide attempts were based on Rudd et al. (2015). A total sample size of 391 (with 52 events) is required to achieve 90% power to detect a hazard ratio of 0.3826 (for survival rates of 0.9240 in the Aviva group [group 1] and 0.8124 in sham app group [group 2] at 18 months), using a one-sided log rank test with 2.5% significance level (i.e.,  $p = 0.025$ ) assuming that the survival rates are exponential and that the total study time is 104 weeks (24 months) with 52 weeks (12 months) accrual.

These results assume that the group sequential design has 3 interim sequential tests (4 total looks including final analysis). The O'Brien-Fleming spending function is used to determine the effectiveness test boundary. See Attachment C: Power Calculation and Group Sequential Design for Aviva Trial – Suicide Attempts (Mathematical Formulations) for full details of sample size calculations.

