#### **11.1.4 Group Sequential Design for Suicide Attempts**

Although the dropouts will not provide the clinical interview information at study end, it will be possible to review hospital records to obtain information regarding suicide attempts by participants (this will be confirmed during informed consent). We will randomize 196 participants to the (Aviva) treatment group and 195 participants to the active control (sham) group and expect to have suicide attempt data for 100% of these participants. We investigated several reasonable variations of the group sequential design and determined that the following is most reasonable. We will test at the 0.025 significance-level (one-sided). The group sequential design has 3 interim sequential tests (4 total looks including final analysis). The looks will occur when 60%, 75%, 90% and 100% of the expected events (i.e., suicide attempts) have occurred. The O'Brien-Fleming spending function is used to determine the effectiveness test boundary. The group sequential design boundaries (on a z scale) are presented in Attachment C.

The power of this GSD is 90%.

Survival analyses will be conducted using the log-rank test for the effectiveness of the intervention on the time to the first suicide attempt after randomization while controlling for censoring effects due to the differential length of follow-up or the completion of follow-up without a suicide attempt. Time to suicide attempt will be measured by calculating the total number of days from enrollment to the first suicide attempt. For participants without a suicide attempt, the total number of days since enrollment to the last assessment will be calculated.

While every effort will be made to track suicide attempts (SA), there may be some missing data. Consistent with standard statistical procedures, missing data are included in the time-to-event analysis as censored observations, with the censoring time at the last contact time with the patient (Friedman et al., 2015).

Estimates of participants making at least 1 subsequent suicide attempt before study end and reattempt-free probabilities at any time point will be derived by the Kaplan-Meier method. The

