The primary effectiveness variable is the time to first suicide attempt (SA) measured from randomization in days. The hazard ratio (HR) reported by Rudd (2015) was 0.3826. Survival curves were estimated using the plot in his paper and the HR of 0.3826. The same HR was taken as the measure of success in the planned trial. The overall study would last up to 2 years (24 months) and accrual would take 12 months. Multiple scenarios were considered and a group sequential test (GST) with a total of 4 Looks as utilized in similar trials was adopted. Sample size calculations and operating characteristics were derived from nQuery (2021). It was agreed that power would be 90% to detect such an HR. Here are the study specifications in the following two tables. Note that the first table includes the sample size estimate and the estimated number of events or patients with a first suicide attempt (SA) post randomization.

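### As worded, section 11.1.4 counts attempts found in records after loss of contact but stops event-free time at last contact. The log-rank test is biased only if loss differs by arm.

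*Protocol*

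**What the plan says.** **What makes an event.** The assessment table in Protocol section 7.1 codes a participant as having attempted suicide if either the SASII or the record review shows it. On the second source it says: "Clinical interviews will be supplemented by a medical record review to identify medically documented SAs during follow up". Sections 7.1, 10 and 11.1.4 all aim this review at participants who do not respond, miss visits or drop out. No section sets a date after which a record-found attempt stops counting.

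**What ends event-free time.** Section 11.1.4 and the synopsis measure participants without an attempt up to the last assessment. The next paragraph of 11.1.4 allows for some missing data and says that "missing data are included in the time-to-event analysis as censored observations, with the censoring time at the last contact time"; the sentence goes on to make clear that contact with the patient is meant.

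**What is expected.** The same section says the trial will "expect to have suicide attempt data for 100% of these participants", and its closing paragraph anticipates no dropout because attempts can be found by several routes.

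**Time origin.** Section 11.1.4 and the synopsis state: "Time to suicide attempt will be measured by calculating the total number of days from enrollment to the first suicide attempt". Attachment C has "time to first suicide attempt (SA) measured from randomization in days", and the endpoint definition in 11.1.1 also starts at randomization.

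**The concern.** After losing contact, a participant can still add an event to the primary analysis but adds no event-free time. Whether follow-up counts then depends on the outcome, which independent censoring does not allow. Each arm's apparent hazard rises with its own rate of lost contact.

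If both arms lose contact equally, the two hazards rise together. The comparison survives, but the Kaplan-Meier rates that the protocol plans to report are too high. If sham loses more, Aviva looks better than it is and the one-sided error exceeds 0.025. If Aviva loses more, power falls.

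The rule also sits badly with the expectation of attempt data for everyone. If records really do cover dropouts, censoring them at last patient contact discards the follow-up on which that expectation rests.

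**Working it through.** **Inputs from the protocol.** Section 11.1.3: "A total sample size of 391 (with 52 events) is required to achieve 90% power to detect a hazard ratio of 0.3826". The 18-month event-free rates given there are 0.9240 for Aviva and 0.8124 for sham, and the log-rank test is run at one-sided 0.025. Attachment C: hazards 0.0115 (sham) and 0.0044 (Aviva) per month, 195 and 196 participants, 12 months' accrual, 24 months' maximum follow-up, drift 3.4387.

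**Assumptions.** Exponential loss of contact, unrelated to attempt risk, with 10% to 30% lost by month 24. Records find all later attempts, or half of them. The only dropout figure in the protocol is 20% per group, for suicidal ideation (Attachment D).

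**1. The plan's own figures reproduce.** Events = 4 × 3.4387² / (ln 0.3826)² = 51.24, rounded up to 52. Event probabilities are 0.1863 (sham) and 0.0760 (Aviva), so 0.1863 × 195 = 36.3 and 0.0760 × 196 = 14.9, against the stated 37 and 15. Dividing 51.24 by the mean event probability gives N = 390.6, hence 391. The sample size is not in question.

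**2. Hand check of the mechanism under HR = 1.** With λ = 0.0115 and follow-up u uniform on 12 to 24 months, the event probability is 0.1863 and mean time at risk is 0.1863 / 0.0115 = 16.20 months. Loss of a proportion p by month 24 has rate δ = −ln(1 − p)/24. With full capture the written rule keeps every event but removes, per participant, the mean over u of e^(−λu) × [u − (1 − e^(−δu))/δ] months of event-free time:

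| Loss | Time removed (months) | Apparent hazard / true hazard |
|---|---|---|
| 10% | 0.575 | 16.20/15.63 = 1.037 |
| 15% | 0.874 | 16.20/15.33 = 1.057 |
| 20% | 1.181 | 16.20/15.02 = 1.079 |
| 25% | 1.498 | 16.20/14.71 = 1.102 |
| 30% | 1.825 | 16.20/14.38 = 1.127 |

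*Equal 20% loss.* The apparent hazard is 0.0115 × 1.079 = 0.0124. The 18-month event rate is 1 − exp(−0.0124 × 18) = 0.200, against a true 1 − exp(−0.0115 × 18) = 0.187.

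*30%/10% sham/Aviva loss.* The null ratio is 1.037/1.127 = 0.92. With 391 × 0.1863 = 72.9 events, the Z shift is −ln(0.92) × √(72.9/4) = 0.356, and P(Z > 1.96 − 0.356) = 0.054.

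*25%/15% loss.* The ratio is 1.057/1.102 = 0.959, the shift 0.177 and the error 0.037.

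**3. Simulation.** Log-rank test at a fixed 24-month cut, 40,000 null trials per row, nominal one-sided 0.025. Rule (a) follows event-free participants to the end of record coverage. Rule (b) cuts events and censoring alike at last contact.

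| Loss, sham/Aviva | Written rule, full capture | Written rule, 50% capture | (a), full capture | (a), 50% capture | (b) |
|---|---|---|---|---|---|
| 20/20 | 0.026 | 0.026 | 0.026 | 0.025 | 0.025 |
| 25/15 | 0.038 | 0.032 | 0.026 | 0.020 | 0.026 |
| 30/10 | 0.058 | 0.039 | 0.026 | 0.016 | 0.026 |
| 15/25 | 0.016 | 0.020 | 0.026 | 0.031 | 0.025 |
| 10/30 | 0.010 | 0.016 | 0.026 | 0.040 | 0.025 |

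Separate simulations of the written rule with full capture gave 0.035 at 25/15 and 0.060 at 30/10.

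**4. Power at HR 0.3826** (Z above 1.96, full capture). At 10/30 loss the written rule lowers power from about 91% to 84–85%; at 30/10 it raises it to 95%. Rule (b) gives 88% to 89%.

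**5. Sequential design.** Using Attachment C's efficacy bounds at 31, 39, 47 and 52 events (8,000 null trials each, full capture, futility not applied), the written rule gives 0.043 to 0.045 at 30/10 and 0.030 to 0.033 at 25/15. At 30/10 a common cut-off gives 0.024. The excess is smaller but remains.

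**The case against.** **The last assessment may include the record review.** Table 1 lists the review among the study assessments through week 104, and section 7.1 names it as one of two methods for assessing attempts. A dropout with a clean week-104 review would then be censored at week 104, and the last-contact sentence would cover only people with neither source. This reading is possible and would remove the asymmetry. The text does not settle it: the missing-data sentence ties censoring to contact with the patient, and nothing says that a clean review extends event-free time. It is a reason to clarify the wording, not to leave it.

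**The SAP could fix censoring dates.** It could, but the protocol has already stated a rule, so this is not simply detail left for later.

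**Differential loss is hypothetical.** This stands. The sham is matched and participants are blinded. The protocol gives no loss rate by arm for the primary endpoint, and its one dropout figure is equal across groups. A reader might infer that the primary test is biased as designed; the documents do not support that.

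**The interim looks.** A reader might also infer bias from record-found attempts counting between widely spaced calls. Table 1 schedules record review at the same visits as the SASII, in both arms, so no arm bias follows from this.

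**The obvious remedy has its own bias.** This stands too. Extending event-free time to the end of record coverage assumes that records find nearly all attempts, whereas the review finds only medically documented ones.

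**Conclusion.** The concern holds as a defect of wording that carries a conditional bias. On its plain reading the rule treats participants with and without an attempt differently after loss of contact.

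- With equal loss, type I error is unaffected and only the event rates are inflated, by about 7% relative at 20% loss.
- With unequal loss the test is biased, in a direction set by which arm loses more. Type I error runs from about 0.01 (10/30) to about 0.06 (30/10) at a fixed 24-month analysis with full capture. At 30/10 it is about 0.04 if records find half of the later attempts.

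These sizes rest on assumed loss and capture rates. They do not show that this trial's error rate exceeds 0.025. The matter is worth settling before the first look because it touches the primary endpoint and costs little. The difference in time origin is a separate, minor inconsistency.

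**What to change.** In the synopsis and section 11.1.4, define one ascertainment cut-off per participant and apply it to events and censoring alike. Two choices are workable:

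- **(a)** the last date covered by a completed SASII or record review, no later than the data cut-off; or
- **(b)** the last completed SASII or contact, with record-found events after that date excluded.

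Pre-specify one as primary and the other as a sensitivity analysis. State explicitly whether the last assessment includes the record review.

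**Costs.** Choice (a) needs the coverage date recorded at reviews already scheduled. If records miss attempts and loss differs by arm, it is biased the opposite way: about 0.015 to 0.040 at 50% capture with 30/10 or 10/30 loss. Choice (b) holds about 0.025 in these simulations, where loss is unrelated to risk, but discards some events and costs roughly 2 to 3 points of power (88–89% against about 91%).

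Separately, measure time from randomization in both places, to agree with 11.1.1 and Attachment C.

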| Rationale for Number of Participants | A total sample size of 391 (with 52 events) is required to achieve 90% power to detect a hazard ratio of 0.3826 (for survival rates of 0.9240 in the Aviva group [group 1] and 0.8124 in sham app group [group 2] at 18 months), using a one-sided log rank test with 2.5% significance level (i.e., $p = 0.025$ ) assuming that the survival rates are exponential and that the total study time is 104 weeks (24 months) with 52 weeks (12 months) accrual. These results assume that the group sequential design has 3 interim sequential tests (4 total looks including final analysis). The O'Brien-Fleming spending function is used to determine the effectiveness test boundary. The study is designed with the expectation that participants will be followed for 104 weeks, but time to event analysis will occur when the expected number of events occur. |

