between-group difference in the proportion of participants making at least 1 repeat suicide attempt by 104 weeks will be evaluated using the asymptotic properties of the Kaplan-Meier estimators of survival probabilities. Although we do not anticipate dropout (because suicide attempt data can be collected via multiple means), this method was chosen to account for dropouts based on the Intent-to-Treat (ITT) principle.

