#### 11.1.5 Secondary Endpoints

SSI will be the first secondary endpoint. Mean changes from baseline will be analyzed using a restricted maximum likelihood (REML)-based repeated measures approach. Analyses will include the fixed, categorical effects of treatment, investigative site, visit, and treatment-by-visit interaction, as well as the continuous, fixed covariates of baseline score and baseline score-by-visit-interaction. Although we will provide training to minimize differences in site, it is recommended the investigative site be included in models of clinical trial data to account for any chance that site-specific subjectivity may influence outcomes (Ting, 2018). A treatment-by-visit interaction allows the effects of the treatment to differ by visit (Ting, 2018). It is reasonable to model the possibility that treatment effects differ by visit because each “dose” of treatment includes different content, study follow-up occurs after treatment has ended, and the study follow-up occurs over an extended period of time. The score-by-visit interaction accounts for the possibility that the impact of baseline to responses at different visits could be different (Ting, 2018). An unstructured (co)variance structure will be used to model the within-subject errors. The Kenward-Roger approximation will be used to estimate denominator degrees of freedom and adjust standard errors. Significance tests will be based on differences of least-squares means using a two-sided  $\alpha=0.05$  (two-sided 95% confidence intervals). Analyses will be implemented using SAS Version 9.4. For SSI, the primary treatment comparison will be the contrast between treatments at 24 weeks. Exploratory models will examine SSI at study end. The same model will be applied for exploratory testing intervention effects on the BDI-II and BHS at study end.

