## Looks-1

## Interim Monitoring & Sample Size Re-Estimation

|                         |                   |
|-------------------------|-------------------|
| GST Parameters          |                   |
| Number of Looks         | 4                 |
| Information Times       | User Input        |
| Max Times               | 1.0000            |
| Efficacy Bounds         | Spending Function |
| Alpha Spending Function | O'Brien-Fleming   |
| Power/HSD Parameter     |                   |
| Truncate Bounds         | No                |
| Truncate At             |                   |
| Futility Boundaries     | Non-Binding       |
| Beta Spending Function  | O'Brien-Fleming   |
| Power/HSD Parameter     |                   |

The combination of the two sets of specifications resulted in the following table:

|                                         | 1       | 2       | 3       | 4        |
|-----------------------------------------|---------|---------|---------|----------|
| Information Time                        | 0.6000  | 0.7500  | 0.9000  | 1.0000   |
| Events                                  | 31.2000 | 39.0000 | 46.8000 | 52.0000  |
| Lower Efficacy Bound                    | -8.0000 | -8.0000 | -8.0000 | -8.0000  |
| Upper Efficacy Bound                    | 2.6686  | 2.3865  | 2.1685  | 2.0748   |
| Futility bound                          | 0.8347  | 1.3133  | 1.7538  | 2.0748   |
| Nominal alpha                           | 0.0038  | 0.0085  | 0.0151  | 0.0190   |
| Incremental alpha                       | 0.0038  | 0.0058  | 0.0085  | 0.0069   |
| Cumulative alpha                        | 0.0038  | 0.0096  | 0.0181  | 0.0250   |
| Exit probability under $H_1$            | 53.1685 | 25.6796 | 15.9430 | 5.2089   |
| Cumulative exit probability under $H_1$ | 53.1685 | 78.8481 | 94.7911 | 100.0000 |
| Nominal beta                            | 0.2019  | 0.0945  | 0.0397  | 0.0190   |
| Incremental beta                        | 0.0337  | 0.0238  | 0.0254  | 0.0171   |
| Cumulative beta                         | 0.0337  | 0.0575  | 0.0829  | 0.1000   |
| Exit probability under $H_0$            | 80.1869 | 12.1123 | 5.9180  | 1.7829   |
| Cumulative exit probability under $H_0$ | 80.1869 | 92.2992 | 98.2171 | 100.0000 |

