**PROPRIETARY AND CONFIDENTIAL**

Oui Therapeutics, LLC | [name]

level to detect a hazard ratio of 0.3826 when the group 1 exponential hazard rate is 0.0115 (this gives a group 2 exponential hazard rate of 0.0044). Under these assumptions, the number of events will be 37 and 15 in group 1 and group 2 respectively. The maximum follow-up time for a subject is 24 time units (months) with an accrual period of 12 time units.

These results assume that the group sequential design has 3 interim sequential tests (4 total looks including final analysis). The O'Brien-Fleming spending function is used to determine the effectiveness test boundary. The O'Brien-Fleming spending function is used to determine the non-binding futility boundary.

The drift parameter for this design equals 3.4387. The drift parameter equals the square root of the maximum information level by the log hazard ratio. The ratio of this drift parameter to the drift parameter from the equivalent fixed term design represents the ratio of the sample sizes required for this GST design to that of its fixed term equivalent.

GST Boundaries (Z scale):

Upper effectiveness bounds: 2.6686, 2.3865, 2.1685, 2.0748

Futility bounds: 0.8347, 1.3133, 1.7538, 2.0748

**ATTACHMENT D***TITLE: Mathematical Formulations for Suicidal Ideation*

PASS 2020, v20.0.3 9/10/2020 2:59:16 PM 1

Two-Sample T-Tests Assuming Equal Variance

Numeric Results for an Equal-Variance T-Test \_\_\_\_\_

 $\delta = \mu_1 - \mu_2$ Hypotheses:  $H_0: \delta = 0$  vs.  $H_1: \delta \neq 0$ 

| Power   | N1  | N2  | N   | $\delta$ | $\sigma$ | Alpha |
|---------|-----|-----|-----|----------|----------|-------|
| 0.83582 | 70  | 70  | 140 | 3.8      | 7.6      | 0.050 |
| 0.88160 | 80  | 80  | 160 | 3.8      | 7.6      | 0.050 |
| 0.91559 | 90  | 90  | 180 | 3.8      | 7.6      | 0.050 |
| 0.94043 | 100 | 100 | 200 | 3.8      | 7.6      | 0.050 |

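### The Kaplan-Meier difference in suicide attempts is fixed at 104 weeks, but the event-driven interim looks are expected before any participant has 104 weeks of follow-up

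*Protocol*

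**What the plan says.** Section 11.1.4 makes the log-rank test on time to first attempt the primary analysis. It also plans an absolute comparison, made with Kaplan-Meier estimates: "between-group difference in the proportion of participants making at least 1 repeat suicide attempt by 104 weeks will be evaluated using the asymptotic properties".

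The timing of the analysis is set by events. The Synopsis (Rationale for Number of Participants) states that "time to event analysis will occur when the expected number of events occur", although it expects participants to be followed for 104 weeks. Section 11.1.4 places looks at 60%, 75%, 90% and 100% of the expected events, and Attachment C converts these to 31.2, 39, 46.8 and 52 events. Attachment C gives the cumulative chance of leaving the trial at each look under the alternative as "53.1685 | 78.8481 | 94.7911 | 100.0000" percent.

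The calendar in section 11.1.3 is "total study time is 104 weeks (24 months) with 52 weeks (12 months) accrual". The sample size is set "to achieve 90% power to detect a hazard ratio of 0.3826". Attachment C states the result "when the group 1 exponential hazard rate is 0.0115 (this gives a group 2 exponential hazard rate of 0.0044" per month, group 1 there being sham.

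**The concern.** A Kaplan-Meier curve has no value at week 104 in an arm where nobody is still under observation at that week. Censoring keeps the log-rank test valid with short follow-up, but it does not supply an estimate at a time beyond the data. Here the landmark equals the whole planned study length, entry is staggered over half of that length, and the design expects to stop early.

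At stake is the absolute effect, the number of attempts avoided, in a trial that section 2.1.2 describes as pivotal. At the stopping analysis the planned figure would usually be missing. Otherwise the last value of the curve would be carried forward and labelled a 104-week result.

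**Working it through.** **Inputs.** Monthly hazards 0.0115 (sham) and 0.0044 (Aviva), 195 and 196 participants, boundaries and exit probabilities (Attachment C); uniform accrual over 12 months (Attachment A); 24 months in total (section 11.1.3); no loss of attempt data (section 11.1.4).

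**1. Reproduce the plan's figures.** For t of at least 12 months, P(event by t) = 1 − [exp(−λ(t−12)) − exp(−λt)]/(12λ). At t = 24:
- Sham: 1 − (0.8711 − 0.7588)/0.138 = 0.1863; × 195 = 36.3 events.
- Aviva: 1 − (0.9486 − 0.8998)/0.0528 = 0.0760; × 196 = 14.9 events.

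The protocol states 37 and 15 after rounding up. Numerical integration of the printed boundaries with drift 3.4387 gives exit probabilities of 53.17%, 25.68%, 15.94% and 5.21% under the alternative, and 90% power. Both agree with Attachment C.

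**2. Expected timing of the looks.** Solve expected events(t) for each count. Longest possible follow-up in weeks = t × 104/24. Share able to reach week 52 = (t − 12)/12, and week 104 = (t − 24)/12, bounded to 0–1.

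| Look | Events | Month | Longest follow-up (weeks) | Can reach W52 | Can reach W104 |
|---|---|---|---|---|---|
| 1 | 31.2 | 16.6 | 72 | 38% | 0% |
| 2 | 39 | 19.4 | 84 | 62% | 0% |
| 3 | 46.8 | 22.3 | 97 | 86% | 0% |
| 4 | 52 | 24.3 | 105 | 100% | 2.4% (about 9 of 391) |

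If both arms had the sham hazard, the looks would fall at about months 13.3, 15.2, 17.2 and 18.5, so even the last would precede month 24.

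**3. Allow for random event timing.** Simulate the full design under the alternative with the log-rank statistic and the printed boundaries, treating a crossing as the end of follow-up. Count a trial as able to give a 104-week difference if each arm has at least one participant at risk at week 104 at the stopping look.
- Both boundaries applied (8,000 trials): 7.3%.
- Futility not acted on: 11.6% in the same simulation; repeat runs lie between 10% and 12%.
- Cross-check: the chances at fixed event counts are 0.1%, 2%, 23% and 51% at the four looks. Weighted by the printed exit probabilities: 0.532 × 0.001 + 0.257 × 0.02 + 0.159 × 0.23 + 0.052 × 0.51 = 0.069.
- No effect, both boundaries applied: 0% if both arms have the sham hazard, 2.4% if both have the mean of the two hazards.
- At week 52 under the alternative: estimable in about 99.9% of trials.

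**4. Vary the assumptions.** The protocol gives no alternatives, so these are assumed. With the same hazard ratio and boundaries, the 7% becomes about 23% with 18-month accrual, 53% with 24-month accrual, 45% with hazards 30% lower, and 71% with 18-month accrual and hazards 30% lower.

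**5. True differences under the design hazards.** Week 104: 0.8998 − 0.7588 = 0.141. Week 52: 0.9486 − 0.8711 = 0.077.

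**The case against.** The strongest reply is that nothing in section 11.1.4 ties the 104-week difference to the look that stops the trial, so it may be meant for complete follow-up. There is support for this. The Synopsis expects 104 weeks of follow-up even though the analysis is event-driven. Section 4.3 ends the trial at the last participant's last contact. Section 9.9 keeps the sponsor blinded until everyone has completed 104 weeks. Inclusion criterion 4 secures two years of record review, and section 11.5 says only that the DSMB may recommend stopping.

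Other text points the opposite way. Section 4.1 plans 104 weeks in total from the first randomization, with 52 of them for enrollment. Section 9.9 also provides for unblinding if the DSMB requires a stop. The objection therefore makes the point conditional but does not remove it, and no later data cut is named for the 104-week difference.

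It is also true that section 11.1.4 allows Kaplan-Meier estimates at any time point and section 11.4 foresees additional ones. A 52-week estimate is thus compatible with the plan, but the formal between-group comparison is still fixed at 104 weeks.

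Some stronger readings are tempting but not supported:
- That nobody can have reached week 104 when the trial stops. This holds for the expected timing of looks 1 to 3, not for look 4 or for trials with slow events, as the 23% and 51% show.
- That the problem remains whatever the calendar. Step 4 shows that it shrinks markedly with slower accrual or lower hazards.
- That the printed exit probabilities alone give the answer. They put 5.2% of trials at the final look under the alternative, which is a different quantity from having someone at risk at week 104.
- That the sentence "Exploratory models will examine SSI at study end" in section 11.1.5 fails in the same way. That section does not define study end as week 104, and the main SSI contrast is at 24 weeks.

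**Conclusion.** The point stands in conditional form. The stated landmark does not fit the event-driven plan: under the design hazards and 12-month accrual, no participant is expected to have 104 weeks of follow-up at looks 1 to 3, where 94.8% of trials stop under the alternative. If a crossing ends follow-up, the 104-week difference has someone at risk in both arms at the stopping look in about 7% of trials under the alternative, or about 10% to 12% if futility is not acted on. These figures rest on exponential hazards, uniform accrual, no loss and that one calendar.

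A reader might infer that the primary result is compromised. It is not: the test "using a one-sided log rank test with 2.5% significance level", its boundaries, alpha and power do not depend on the landmark. The defect is a stated rule for the absolute effect that would usually give a missing or mislabelled result, together with conflicting statements on follow-up after a stop.

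**What to change.** In section 11.1.4, evaluate the Kaplan-Meier between-group difference at 52 weeks at whichever look stops the trial. Report a 104-week difference only from a later data cut in which participants have completed 104 weeks. Reconcile the Synopsis and sections 4.1, 4.3 and 9.9 on whether follow-up continues after a stop. The futility bound should be reconciled with them, since the Synopsis and section 11.5 call it binding while section 11.1.1 and Attachments A and C call it non-binding.

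The change is to wording only, but it has two costs. The horizon is shorter, with a true difference of 0.077 in place of 0.141. The 52-week estimate is also inflated in trials that stop early for efficacy: at look 1 it averages about 0.105 against 0.077, roughly a third too high, although coverage of the nominal 95% interval stays near 95%. The report should state this when the trial stops early.
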